## Conclusion

KOA is a chronic degenerative joint disease that causes joint pain and dysfunction. The main objective of KOA treatment is to reduce pain and improve dysfunction, in which physical factor treatment is an important intervention [40]. In this study, changes in cerebral cortical blood flow measured by fNIRS were used to evaluate changes in brain activation status in normal subjects and KOA patients and the consistency with the severity of pain in KOA patients. In addition, we will evaluate the effect of physical factor therapy on pain and dysfunction in KOA patients based on fNIRS.

The study will be conducted in the Rehabilitation Medical Center of West China Hospital of Sichuan University, and patients will be enrolled through poster recruitment and outpatient registration. This study is a noninvasive, adaptive and innovative way to evaluate the effectiveness of physical therapy in KOA patients.

FNIRS is an innovative neuroimaging technique for measuring hemodynamic changes during brain activation [41]. fNIRS has the characteristics of portability, wireless nature and lightweight, which can be used as an objective index to evaluate changes in pain [42]. A recent study used fNIRS to evaluate the effect of exercise on the severity of pain, and the results showed that there was a significant difference in the activation of the prefrontal cortex before and after exercise [22]. However, there is currently no study comparing changes in cerebral hemodynamics between healthy subjects and KOA patients and whether changes in cerebral hemodynamics are used as objective indicators of pain and functional improvement in KOA patients.

Therefore, the advantages of this study are mainly summarized as follows: (1) On the basis of previous studies, healthy subjects were added to evaluate the degree of cerebral cortex activation in healthy subjects; (2) evaluating the changes in cerebral blood flow between KOA patients with different pain severities and to provide an experimental basis for fNIRS as an objective index for the clinical pain evaluation of KOA patients; and (3) After using physical factors to treat KOA patients, we compared the changes in cerebral blood flow, NRS, and functional activity scores between different groups of KOA patients under different action instructions.

However, there are still some limitations in the design of this study: (1) This study has not yet conducted a follow-up survey, so it cannot evaluate the long-term therapeutic effect of physical factor therapy on pain and dysfunction in KOA patients; (2) In view of the nature of physical therapy in clinical research, it is difficult to achieve a double-blind experimental process (the therapist blind method and the subject blind method). In conclusion, the results of this study provide an important objective evaluation index for physical factor therapy to improve the dysfunction of KOA patients and extend a new perspective for fNIRS as a new objective clinical diagnostic index for KOA.

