## Abstract

**Background:**

Knee osteoarthritis (KOA) is a chronic musculoskeletal disease that can cause joint pain and dysfunction, affecting the quality of life of patients. Nonsurgical treatment is the conventional treatment of KOA, among which physical therapy is widely used because of its simplicity, convenience and effectiveness. The functional biomarker will add to the clinical fidelity and diagnostic accuracy. Therefore, our study chose a more objective evaluation indicator, functional near-infrared spectroscopy (fNIRS), to identify between healthy people and KOA patients, and to detect the pain change before and after treatment of KOA patients.

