**Methods:**

The study will be conducted in the Rehabilitation Medical Center of West China Hospital of Sichuan University and divided into 2 stages. In the first stage, we will compare and determine the differences in baseline data between healthy volunteers and KOA patients. In the second stage, 72 KOA patients will be randomly divided into two groups: the drug therapy group (DT) and the combination therapy group (CT) for 10 treatments. Outcome measures will be measured at baseline and on the 5th and 10th days after the intervention, including the numerical rating scale (NRS), Western Ontario and McMaster Universities Osteoarthritis Index (WOMAC), pain catastrophizing scale (PCS), the association of pain severity with task-state functional connectivity fNIRS and association of pain severity with task-activated fNIRS.

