## Methods

The trial will be divided into two stages. The first stage is to analyze the baseline data of healthy volunteers and KOA patients and compare the differences between the two groups. In the second stage, the KOA patients will be randomly divided into two groups, and the outcome indicators will be analyzed after the intervention. This stage is a single-center, single-blinded, parallel randomized controlled trial (RCT). The trial will follow the Recommendations for Interventional Trials [24], and the flow diagram is shown in Fig. 1. The trial will be conducted in West China Hospital, Sichuan University, Chengdu, China. All participants will sign written informed consent forms.

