### Participants

Two trained rehabilitation physicians will recruit 24 healthy volunteers over 50 years old and 72 KOA patients according to the inclusion and exclusion criteria. Patients should meet the following conditions: (1) diagnosed with KOA according to the 2021 Chinese Orthopedics Association diagnosis and treatment guidelines [25]; (2) knee pain (previous week) score ≥ 3 on the NRS; (3) Kellgren–Lawrence grade I-III [26]; (4) right-handed; (5) normal lower limbs; and (6) no open wounds or metal foreign bodies near the knee joint.

The exclusion criteria were as follows: (1) diagnosed with rheumatoid arthritis, gout or severe osteoporosis; (2) having undergone knee surgery or received an intra knee injection within the past 6 months; (3) experiencing depression (using the Self-rating depression scale, depression severity index < 0. 50 is no depression [27]), anxiety (using the Self-rating Anxiety Scale, standard score < 50 is no anxiety [28]), mania (using the Bech-Rafaelsen Mania Scale, ≤ 5 is no mania [29]), dementia and obvious cognitive impairment (using the Montreal Cognitive Assessment, ≥ 26 is normal [30]); (4) having a cancerous tumor, severe bronchiectasis, acute suppurative inflammation, high fever, active pulmonary tuberculosis, glaucoma, heart failure, severe anemia, cerebrovascular disease, or having a pacemaker implanted in the body; (5) having a history of epilepsy or taking antiepileptic drugs; (6) taking drugs that change the excitability of the cerebral cortex (such as sedative-hypnotics or antidepressants); (6) unable to participate in the trial due to other health problems; and (7) unable to sign the informed consent or participate in other scientific research projects(for example, a sudden fall, sudden low back pain, shoulder pain and other sudden diseases).

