## Statistical analysis

Data analysis will use an intention-to-treat analysis strategy. Data analyses will use SPSS (26.0). P ≤ 0.05 will be significantly different. The raw data collected by fNIRS will be preprocessed by NIRSPARK software, including artifact processing, filtering, segmentation and baseline comparison. At the same time, the fNIRS data will be analyzed using the statistical analysis module of MATLAB (R2020a). Component comparability of baseline data between the two groups will be performed using the chi-square test and independent samples t test. The frequency and percentage of count data will be calculated in the statistical description; the data of measurement data following a normal distribution will be described by the mean ± standard deviation. For the comparison between groups after the intervention, the independent samples t test will be used if the data follow a normal distribution, and the Mann‒Whitney U rank sum test will be used if the data are nonnormally distributed. For intragroup comparisons before and after the intervention, a paired t test will be used if the data follow a normal distribution, and the Wilcoxon rank sum test will be used for data that are not normally distributed.

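### The article aims to identify KOA patients with fNIRS and closes on a diagnostic index, but describes stage 1 only as a group comparison, which does not measure discrimination

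*Protocol article*

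**What the plan says.** **The claim.** The Background part of the Abstract states that "The functional biomarker will add to the clinical fidelity and diagnostic accuracy" and gives as a reason for choosing fNIRS that it is "to identify between healthy people and KOA patients". The last sentence of the Conclusion expects the results to "extend a new perspective for fNIRS as a new objective clinical diagnostic index for KOA".

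**The stage 1 analysis.** The opening of Methods says: "The first stage is to analyze the baseline data of healthy volunteers and KOA patients and compare the differences between the two groups". The Abstract agrees: "we will compare and determine the differences in baseline data between healthy volunteers and KOA patients". Under Interventions, stage 1 participants receive no treatment and are measured once.

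**The named methods.** The Statistical analysis section says: "Component comparability of baseline data between the two groups will be performed using the chi-square test and independent samples t test". It then gives t or rank tests for comparisons between groups after the intervention and for changes within a group. The fNIRS data are assigned to a MATLAB module with no method named. The article mentions no ROC curve, AUC, sensitivity, specificity, cut-off or validation step.

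**Who is compared.** Participants lists 24 healthy volunteers over 50 and 72 KOA patients, who must have "knee pain (previous week) score ≥ 3 on the NRS". Under Sample size, the 24 come from a 3:1 ratio.

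**The concern.** Telling patients from healthy people is a question about individuals: given one person's fNIRS reading, how often is that person placed in the right group? A comparison of differences asks whether two groups differ on average. Two distributions can differ clearly in mean and still overlap so much that few individuals are classified correctly.

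The choice of groups adds a second limit. A diagnostic index is used in people whose diagnosis is uncertain. Stage 1 compares people without the disease with patients who already have the diagnosis and a minimum level of pain. Separation between those two groups does not show accuracy in people who are being investigated for KOA.

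What is at stake is the reading of stage 1. A difference between the groups could be taken as support for a diagnostic use that neither the described analysis nor the comparison can establish. The randomized NRS comparison in stage 2 is not affected.

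**Working it through.** **Inputs from the article.** 72 KOA patients and 24 healthy volunteers (Participants; Sample size), and a significance level of 0.05 (Sample size; Statistical analysis).

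**Assumptions.** The test is two-sided, since the article does not say. The fNIRS summary is normally distributed with equal variances in the two groups. The article gives no fNIRS mean, SD or effect size, so everything is expressed as a standardized difference d.

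**1. The article's own figure.** 72 / 3 = 24 healthy volunteers. This reproduces. It follows from a ratio and not from a target for discrimination or precision.

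**2. Smallest difference that reaches P = 0.05.**
d = t(0.975, 94 df) × √(1/24 + 1/72) = 1.9855 × √0.05556 = 1.9855 × 0.2357 = 0.468.

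**3. What that difference means for classification.**
- AUC = Φ(d/√2) = Φ(0.331) = 0.63
- Sensitivity = specificity at the midpoint cut-off = Φ(d/2) = Φ(0.234) = 0.593, about 59%

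Chance would be 0.50 and 50%.

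**4. Larger differences.** The first row is an observed difference. The next two are true differences detectable with the stated power at 24 versus 72.

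| Case | d | AUC | Sensitivity = specificity |
|---|---|---|---|
| Just significant (observed) | 0.468 | 0.63 | 59% |
| 80% power (true) | 0.667 | 0.68 | 63% |
| 90% power (true) | 0.772 | 0.71 | 65% |
| AUC of about 0.80 | 1.2 | 0.80 | 73% |

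So even a true difference that the comparison would detect nine times in ten goes with an AUC of only about 0.71.

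**5. Precision if an AUC were reported.** Hanley–McNeil standard error with 72 patients and 24 controls, at A = 0.75:
- Q1 = A/(2 − A) = 0.600
- Q2 = 2A²/(1 + A) = 0.643
- SE = √{[A(1 − A) + 71(Q1 − A²) + 23(Q2 − A²)] / (72 × 24)} = √{[0.1875 + 2.6625 + 1.8482] / 1728} = 0.052
- 95% CI = 0.75 ± 1.96 × 0.052, about 0.65 to 0.85

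Specificity rests on the 24 controls alone. If 20 of 24 (83%) were classified correctly, the exact 95% CI would be 63% to 95%.

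**6. Selection of patients.** No arithmetic applies. The NRS threshold and the healthy comparator are fixed by the design, so no choice of statistic turns the comparison into one among people with suspected disease.

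**The case against.** There are four serious counterarguments.

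- **The tests may not belong to stage 1.** The rank test is given for comparisons after the intervention, which healthy volunteers do not receive. The two groups in the baseline sentence may be the two treatment arms. The fNIRS method is left to an unnamed MATLAB procedure. This stands. A reader might infer that the plan commits stage 1 to tests of means and nothing else, but the article does not say that. What it does say is that stage 1 compares differences, and it ties no discrimination measure to the stated aim.
- **A fuller protocol or analysis plan may contain an ROC analysis.** That is possible, and the absence of an AUC from a condensed article would not be a finding by itself. The point rests on the article's pairing of an identification aim and a diagnostic phrase with a stage described as a group comparison. An unseen plan also could not change who is compared.
- **The closing phrase is hedged, and most fNIRS aims concern pain severity.** Both are true. The listed fNIRS outcomes are associations with pain, and a group comparison does answer the question as Methods frames it. A reader might infer that P ≤ 0.05 will be reported as proof of diagnostic value, but no such rule is written. The Abstract's identification aim, however, is stated without that hedge.
- **The just-significant case is the least favourable significant result.** It is. That is why the 80% and 90% power rows are shown; they change the degree and not the conclusion.

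A reader might also infer that the best of 40 channels, or of 160 channel-task pairs (40 × 4), will be picked out and will seem to discriminate by chance. The article describes no such search, and any figure for it would need an assumption about how channels correlate. This point does not rely on it.

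**Conclusion.** The concern holds as a mismatch between a stated aim and the analysis described for it. A difference between 72 selected patients and 24 healthy volunteers can be statistically significant with an AUC of about 0.63 and about 59% sensitivity and specificity. Those figures assume normality, equal variances and a two-sided 5% test; the article supplies no fNIRS data against which to check them. The limit on who is compared needs no such assumption: even excellent separation here would not show accuracy among people with suspected KOA. The article should be changed, but the problem is confined to what stage 1 can be said to show.

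**What to change.** 1. For the identification aim, name one fNIRS summary in advance (for example, mean oxyhaemoglobin change in one region during one task). Report its AUC with a 95% CI alongside the group comparison, and state which test that comparison uses.
2. Label results for any other channel or task as exploratory.
3. Replace the closing phrase about a diagnostic index with *discrimination between healthy volunteers and patients with symptomatic KOA (NRS ≥ 3)*, and bring the Abstract's remark on diagnostic accuracy into line.

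The cost is a few lines of text, with no extra participants or measurements. The price is a narrower claim and, with 24 controls, an interval wide enough that stage 1 will give only a rough estimate of discrimination.

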## Data Availability

The datasets used and/or analyzed during the current study are available from the corresponding author on reasonable request.

## Abbreviations

KOA: Knee osteoarthritis
fNIRS: Functional near-infrared spectroscopy
DT: Drug therapy group
CT: Combination therapy group
NRS: Numerical rating scale
WOMAC: Western Ontario and McMaster Universities Osteoarthritis Index
PCS: Pain catastrophizing scale
OA: Osteoarthritis
QoL: Quality of life
LIPUS: Low-intensity pulsed ultrasound
tDCS: Transcranial direct current stimulation
RCT: Randomized controlled trial
MICD: Minimum clinically important difference
M1: Motor Cortex
SMA: Supplementary motor area
tDCS: Transcranial direct current stimulation
